### Quantitative data analysis

We will use descriptive statistics to analyse the feasibility outcomes; these will include the distribution of scores, mean, standard deviation, medians, frequencies, and percentages. Qualitative and quantitative data will be triangulated to validate their findings and provide a more in-depth understanding regarding what is observed.

be measured using a combination of descriptive and inferential statistics. Eligibility assessment will be quantified by calculating the proportion of screened individuals who meet inclusion criteria. Recruitment rates (number of eligible participants screened divided by number of participants consented) and pathways will be analysed using frequency distributions to determine the most effective channels for enrolment of the older adults with intellectual disability. The consent rate will be measured as the percentage of eligible adults with intellectual disability who agree to participate. The overall retention rate will be calculated as the proportion of older adults with intellectual disability completing the study. These measures collectively inform the feasibility of implementing and scaling the Matilda intervention effectively for a definitive RCT [49, 50].

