## Methods

### Study design

This is a 2-arm, single-blind, randomised feasibility study with 1:1 allocation, which will be conducted in Northern Ireland and London (Fig. 1). Sixty-four older adults with an intellectual disability will be randomly allocated to either the Matilda intervention plus usual care (‘usual care’ in this instance refers to participants attending a day centre or day opportunity setting) or usual care with three group recreational activities with other older adults with an intellectual disability (active control arm). Group recreational activities will involve older adults with an intellectual disability in the active control arm meeting together on three occasions for example for a meal, a coffee or bowling, etc.

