### Progression criteria

We will apply predetermined progression criteria as set by Avery et al. [34]. This will be based on the feasibility outcome data pertaining to recruitment, matching older adults with an intellectual disability to mentors, retention rates and reasons for attrition, programme attendance, protocol adherence, and the completion of outcome measures. We will monitor recruitment rates in each site. We will have a wide recruitment network from the outset including user-friendly information on how to promote the study and meetings with various local community organisations. We will identify champions in both sites to help study promotion and a process evaluation will take place with stakeholders.

A traffic light system (green, amber, red) will be used to inform whether the study should progress to a full trial, whether revisions are required, or whether it should be stopped. If there is efficacy, and the green progression criteria are met, it would be appropriate to move to a definitive trial, see Table 1.

**Table 1 Tab1:** Progression criteria: a traffic light system

Progression criteria	Red	Amber	Green
1) Recruitment rates of adults with an intellectual disability and mentors who are approached consenting to randomisation across both sites	<39%	40–69%	70% plus
2) Acceptability of and engagement in the Matilda intervention of at least 60% of the adults with an intellectual disability allocated to this arm across both sites	<39%	40–59%)	>60%
3) Acceptability of the matching process, and engagement in the Matilda intervention of at least two mentors for at least 60% allocated to this arm across both sites	<39%	40–59%)	>60%
4) Acceptability of the appropriateness of the outcome measures for at least 60% of the adults with an intellectual disability and their mentors across both sites	<39%	40–59%)	>60%
5) Retention of at least 60% of the recruited adults with an intellectual disability and their mentors at the 6- and 12-months follow-up across both sites	<39%	40–59%)	>60%

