### Sample size

The chosen sample size is justified based on feasibility outcomes, specifically estimating the proportion of adults with intellectual disability who are recruited and retained. With 64 participants, if observed retention is 60%, the 95% CI for the true proportion retained would be approximately 46% to 71%.

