### Fidelity of intervention

We will collect information in the screening logs on how many eligible adults with an intellectual disability were randomised or the reasons for exclusion of those who were assessed for eligibility.

A checklist will be further developed to explore the fidelity of the Matilda intervention in greater detail in the process evaluation. In assessing the external validity, the extent of true collaboration in each local community group initiative will be assessed with the adults with an intellectual disability, carers, and mentors. To determine whether the Matilda intervention will be delivered as intended (adherence), each mentor will be asked to complete their own weekly paper checklist, which details attendance, frequency, activities, adverse events, etc.

We will measure the frequency of the delivery of the Matilda intervention monthly through the logs, process evaluation, and acknowledge the variability of the groups. Where possible, all the adults with an intellectual disability allocated to the intervention arm will be afforded the opportunity to access a group for the full 6-months. There may be occasions where some adults with an intellectual disability do not access their group, and this will be explored and recorded.

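### Progression criterion 1 grades recruitment per person approached, but the analysis section builds its recruitment rate on eligible adults and omits mentors, so one go/no-go rate has two definitions

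*Protocol article*

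**What the plan says.** **Progression criteria, Table 1, criterion 1.** The graded quantity is "Recruitment rates of adults with an intellectual disability and mentors who are approached consenting to randomisation across both sites". The bands are printed as red below 39%, amber 40–69% and green 70% or more. The base is people approached, and it covers both adults with an intellectual disability and mentors.

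**Quantitative data analysis.** Three rates bear on recruitment:
- Eligibility: "Eligibility assessment will be quantified by calculating the proportion of screened individuals who meet inclusion criteria".
- Recruitment: "Recruitment rates (number of eligible participants screened divided by number of participants consented".
- Consent: "The consent rate will be measured as the percentage of eligible adults with intellectual disability who agree to participate".

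**Fidelity of intervention.** On the source of the counts: "We will collect information in the screening logs on how many eligible adults with an intellectual disability were randomised". The same sentence adds the reasons for exclusion among those assessed. It does not mention a count of people approached.

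**Study design.** "Sixty-four older adults with an intellectual disability will be randomly allocated". Under Randomisation and assignment of interventions, only adults with an intellectual disability are randomised.

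**The concern.** The same term, recruitment rate, has one definition where it is graded and another where it is calculated. Table 1 divides by people approached. The analysis section uses eligible screened adults and consented adults, and people approached do not appear.

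The protocol's own procedures let these groups differ. Inability to consent and existing attendance at a mainstream community group are both exclusions. The Consent section has the Research Associate assess capacity in conversation with the person, so some people can be found ineligible only after they have been approached. A rate based on eligible adults leaves those losses out; a rate based on people approached counts them.

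Criterion 1 is one of five that decide whether the trial progresses, is revised or stops. Two analysts, one following Table 1 and the other following the analysis section, could report different lights from one screening log.

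**Working it through.** **The plan's own figure.** The article states no expected recruitment rate to reproduce. Its only precision figure concerns retention: "With 64 participants, if observed retention is 60%, the 95% CI for the true proportion retained would be approximately 46% to 71" per cent. An exact (Clopper-Pearson) interval on 38/64 = 59.4% gives 46.4% to 71.5%, which agrees. The present point does not depend on it.

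**Inputs.** From the article: 64 adults, taken here as the number consenting, and cut-offs of 40% and 70%. I apply the cut-offs unrounded and treat anything below 40% as red. Not in the article, so assumed: the number approached and the number eligible. Mentors are left out of the arithmetic because no mentor counts are given.

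**Step 1: the recruitment rate as printed.** Eligible screened / consented. With 85 eligible and 64 consenting, 85/64 = 133%. If every consenter is an eligible screened adult, this ratio cannot fall below 100%, so it would always be green and cannot be what Table 1 grades.

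**Step 2: the fraction turned over.** Consented / eligible = 64/85 = 75%. This is the consent rate already defined in the next sentence, so the section then has one rate under two names.

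**Step 3: Table 1's rate for adults.** Consented / approached. If 100 were approached to find those 85, 64/100 = 64%. One log gives green in step 2 and amber here.

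**Step 4: where the lights change with 64 consents on the approached base.**
- Green limit: 64/91 = 70.3% and 64/92 = 69.6%, so at most 91 approached. (If rates were rounded to whole per cent first, 92 would also pass.)
- Amber floor: 64/160 = 40.0%, so red beyond 160 approached.

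**Step 5: range.** When all eligible adults come from those approached,

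consented/approached = (consented/eligible) × (eligible/approached).

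| Consented/eligible (light) | 90% of approached eligible | 70% eligible | 40% eligible |
|---|---|---|---|
| 60% (amber) | 54% amber | 42% amber | 24% red |
| 70% (green) | 63% amber | 49% amber | 28% red |
| 80% (green) | 72% green | 56% amber | 32% red |
| 90% (green) | 81% green | 63% amber | 36% red |

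The colour differs between bases in 8 of these 12 cells. It stays the same when nearly everyone approached is eligible, or when the eligible-base rate sits well inside its band.

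**Step 6: can the defined rates be combined?** (Eligible/screened) × (consented/eligible) = consented/screened. This equals criterion 1 for adults only if everyone approached is screened, which the article does not say.

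**The case against.** The strongest reply is that Table 1 already states its event and its base. The analysis section nowhere says that its descriptive rates are the values graded; it offers them as jointly informing feasibility. Reporting consent among eligible adults beside a criterion based on people approached is not in itself an error. This stands in part: a reader might infer that the denominator is open and can be chosen once the data are seen, but that would require the analyst to depart from Table 1. What remains is that the analysis section gives the criterion's own term, recruitment rate, a different and inverted formula.

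Three other strong readings are also unsupported:

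- **That both rates in the analysis section use eligible adults as the base.** As printed, only the consent rate does. The recruitment rate has consented adults in its denominator and acquires the eligible base only once it is turned over.
- **That the section can never yield criterion 1.** The product in step 6 recovers it for adults if everyone approached is screened. The article neither says nor excludes this. A health and social care provider confirms eligibility at an unstated time; if that precedes approach, the two groups largely coincide and the gap shrinks.
- **That the discrepancy could equally run the other way, with eligible adults never approached.** This fits the text poorly. Ability to consent is part of eligibility and is assessed with the person.

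It is also fair to say that log fields and operational definitions usually sit in the full protocol or analysis plan, which are not shown. Their absence from the article is not the complaint. The complaint is that two definitions the article does print disagree.

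**Conclusion.** The point holds as a conflict of definitions in a go/no-go criterion. Table 1 grades recruitment per person approached, for adults and mentors. The analysis section gives the same term a formula on eligible and consented adults, prints it inverted, and defines nothing per person approached and nothing for mentors.

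The size is conditional. On the assumed 85 eligible among 100 approached, the light moves from green (75%) to amber (64%). Across the assumed range, it changes in most cells once 70% or fewer of those approached are eligible. The article gives no counts, so nothing here shows that the trial's light will in fact be wrong. The mismatch should be settled before criterion 1 is read. Trial status reports recruitment completed in March 2024, so the counts may already be known.

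**What to change.** 1. Let Table 1's base govern. In Quantitative data analysis, define the recruitment rate as adults with an intellectual disability consenting to randomisation / adults with an intellectual disability approached, graded against 40% and 70%. This also removes the inverted fraction.
2. Give mentors a separate rate: mentors consenting to take part / mentors approached. They are not randomised, so consent to randomisation does not describe them. State how this rate enters criterion 1, so that mentors are not dropped unannounced.
3. Keep consented / eligible as a descriptive consent rate.
4. Report the approached, screened, eligible and consented counts, so that a reader can compute either rate.
5. If the number approached was not logged, say so and name the substitute (for example, adults screened) before the light is read.

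**Cost.** Items 1 to 4 need a few sentences and no change to trial conduct, provided the number approached was kept. Recruitment is over and the article mentions no such count, so it may not be recoverable; item 5 covers that case. The other downside is that the rate may look less favourable than on the eligible base.

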### Qualitative data analysis

These focus groups will be audio recorded and transcribed, stored via NVivo software and analysed using the 6-stage process by Braun and Clarke [51] a deductive thematic analysis. To ensure the quality of the data and trial, we will establish an independent Trial Steering Committee (TSC) and an independent Data Monitoring Ethics Committee (DMEC), which consists of experts outside this feasibility study.

### Health economics evaluation

The economic evaluation will explore issues likely to be encountered in the conduct of a full economic appraisal, including sources of data, how best to collect these, and the inclusion of spill-over effects into the analysis. We will assess the feasibility of calculating quality adjusted life years (QALYs) using both the EQ5DY and WHOQOL-DIS and including spill-over effects experienced by mentors and carers in the evaluation.

Costs of providing the intervention (including recruitment, training, and expenses related to the supervision by the project manager) will be collected from the project manager in collaboration with participating sites. Information on resource use will be collected using an adapted version of the Client Service Receipt Inventory. Data will be collected at baseline, 6 and 12 months post-intervention. Resource utilization will cover the period since the last data collection point at 6 and 12 months: and in the previous 6 months in the case of baseline measurement. Health and social care use will include contacts with health professionals such as GPs, psychiatrists, psychologists, community nurses, social workers, and community intellectual disability teams, as well as use of hospital accident and emergency, inpatient, and outpatient services. Information on prescription of medicines will also be collected.

Resource use will be monetised using published sources, PSSRU [52], NHS reference costs [53] and the British National Formulary [54]. Costs will be reported from a health and social care perspective. In the base case analysis, we will focus on costs and outcomes as they accrue to the participant with an intellectual disability only. Total costs in each randomised group will be compared using a Generalised Linear Regression Model as costs are likely to be non-zero and positively skewed.

We will explore estimation of the incremental mean cost per QALY gained from the intervention compared to the control group and the cost-effectiveness of the intervention across other outcome measures. If calculable, the mean QALY per participant with an intellectual disability will be calculated as the area under the curve for the duration of the trial, adjusting for baseline values. CIs will be constructed using non-parametric bootstrapping with replacement. This exercise will be explored for outcome measures generated using EQ5D if possible and cost-effectiveness using WHOQOL-DISF.

## Discussion

In partnership with our PPI organisation, CAN Advocacy Support Network, we have seen strong enthusiasm from older adults with intellectual disabilities who value opportunities to join local community groups and form new friendships. Likewise, community organisations have expressed willingness to welcome and support inclusion. The MATILDA feasibility trial will build on this momentum, extending earlier work to understand how community networks can be strengthened and what practical supports are needed for mentors and groups to sustain engagement.

Beyond testing feasibility, MATILDA contributes to the broader implementation science agenda by examining how inclusive community models can be embedded within existing infrastructures and sustained over time. Using implementation frameworks will help identify barriers and enablers to adoption, assess readiness for change, and generate learning relevant to future commissioning and policy reform. In doing so, MATILDA aligns closely with the NIHR Implementation Science priorities and UK policy directives such as NICE NG96 and the Adult Social Care Reform White Paper, which advocate for scalable, community-based approaches that promote independence, inclusion, and wellbeing.

However, feasibility challenges are anticipated. Recruitment may be constrained by the availability of suitable mentors and the capacity of services to identify eligible participants. The sample, drawn from specific UK contexts, may limit generalisability. In addition, the evolving post-pandemic environment continues to affect community participation and volunteer engagement. Addressing these challenges will be critical to refining recruitment pathways, support structures, and intervention delivery ahead of a definitive trial.

## Trial status

Protocol version 5.0, 28/12/2023. Recruitment started in June 2023 and completed in March 2024. Data collection commenced in June 2023 and will continue through to June 2025.

## Data Availability

Not applicable.

## Abbreviations

MATILDA: Managing Activities Together, to Involve older adults with a Learning Disability in their local community
PIS: Participant Information Sheet
PPI: Patient and Public Involvement
RA: Research Associate
RCT: Randomised controlled trial
TTR: Transition To Retirement
